## Abstract

*Background and Objectives*: The Quantum Menstrual Health Monitoring Study will measure four key reproductive hormones in the urine (follicle-stimulating hormone, FSH; estrone-3-glucuronide, E_1_3G; luteinizing hormone, LH; and pregnanediol glucuronide, PDG) to characterize patterns that predict and confirm ovulation, referenced to serum hormones and the gold standard of the ultrasound day of ovulation in participants with regular cycles. These normal cycles will provide a reference for comparison to irregular cycles in subjects with polycystic ovarian syndrome (PCOS) and athletes. *Materials and Methods*: Participants will track their menstrual cycles for 3 months and be provided with an at-home urine hormone monitor (Mira monitor) to predict ovulation. The day of ovulation will be confirmed with serial ultrasounds completed in a community clinic. Urine results will be compared to serum hormone values. Other markers of menstrual health, such as bleeding patterns and temperature changes, will be determined using a customized app. Three groups will be recruited. Group 1 will include those with consistent regular cycle lengths (between 24–38 days), and will be compared to two groups with irregular cycle lengths (with increased cycle length variability and longer cycles). Group 2 will include those with polycystic ovarian syndrome (PCOS) with irregular cycles and Group 3 will include individuals participating in high levels of exercise with irregular cycles. *Hypothesis*: The Mira monitor quantitative urine hormone pattern will accurately correlate with serum hormonal levels and will predict (with LH) and confirm (with PDG) the ultrasound day of ovulation in those with regular cycles as well as those with irregular cycles. *Rationale*: Once the ultrasound validation is complete, tools like the Mira monitor with a customized app may become a new standard for at-home and remote clinical monitoring of the menstrual cycle without having to use labor-intensive follicular-tracking ultrasound or follow serum hormone changes. *Conclusions*: Precision monitoring of the menstrual cycle is expected to impact individuals who want to increase their menstrual health literacy and guide decisions about fertility.

## 1. Introduction

### 1.1. Background

The menstrual cycle has been described as the “fifth vital sign” by professional associations [1], menstrual cycle researchers [2], and popular literature [3], reflecting a complex interaction between the hypothalamus, pituitary, and ovaries [4] (Figure 1). Observing this “vital sign” in a regular cycle can provide reassurance about the homeostasis of the reproductive system [2,4], while self-measured menstrual cycle changes could help to identify pathological states. Long and irregular menstrual cycles with anovulation are often reflective of underlying polycystic ovarian syndrome (PCOS) [5], which affects approximately 10% of reproductive-aged women [6]. Similar cycle disturbances are also present in athletes [7]. Other physiologic variations like the postpartum period [8] and perimenopause [9] have also been followed with menstrual cycle tracking [8,10]. There is, however, a significant gap in general knowledge of the menstrual cycle [11], and improving menstrual literacy [11,12] could be helpful for the common problem of infertility in North America [13], where the substantial need for care [14] may include both specialized care [15] and primary care approaches to infertility [16]. A simple primary care approach could include educating couples on the timing of intercourse with a personalized, at-home evaluation of urinary hormones [17]. Menstrual cycle hormones are usually evaluated with serum measurement of the key reproductive hormones shown in Figure 1; however, the complex dynamics of these hormones are inter-related on a day-to-day basis, so a single serum value in the cycle is less valuable than daily variations, which are more amenable to pattern recognition using urine hormones measured at home.

### 1.2. Irregular Cycles

PCOS is known to cause long and irregular menstrual cycles, related to an underlying ovulatory dysfunction [5,18]. Treating conditions like PCOS [19] can substantially improve couples’ chances of conceiving. PCOS is known to be associated with the development of endometrial cancer in diverse populations of women [20,21,22], likely driven by unopposed estrogen [23]. If women can identify this unopposed estrogen early on by monitoring their menstrual health, they may be able to address this pathology earlier to reduce the burden of this effect on endometrial cancer risk.

It seems obvious that the menstrual cycle may affect athletes’ performance, yet research efforts are needed to document how it does so to enable athletes and coaches to use the knowledge in training and performance plans [24]. It may also shed light on variability in the menstrual cycle. The menstrual cycle is not just perceived to influence the female athletes who experience it, but it also has excluded them from being used in scientific studies because it produced “white noise” in the results [7]. There is the possibility that we may improve aspects of physiological and psychological performance by understanding and monitoring athletes’ menstrual patterns, yet the quality of the literature regarding physiological effects has been criticized for inappropriate verification of the menstrual cycle phase [25]. In both circumstances, of PCOS and athletic menstrual cycle disturbances, menstrual cycle monitoring could serve as an “early warning system” to identify cycle disturbances.

### 1.3. Menstrual Cycle Monitoring

Digital health and personalized medicine are advancing at an unprecedented pace. There are now over one thousand smartphone apps to evaluate the menstrual cycle [26], but multiple studies in Canada and elsewhere have demonstrated that most of these apps are inaccurate [26,27,28]. Many people are searching for a more in-depth knowledge of the menstrual cycle [11], which fuels the high demand for these smartphone Apps, yet most of the apps available are unlikely to significantly improve users’ menstrual health literacy [29,30]. A second challenge with menstrual cycle apps is a lack of security and privacy, with some major apps having had data breaches for sharing users’ data [31], demonstrating the importance of ensuring these technological tools align with users’ best interests [32,33].

In addition to menstrual cycle apps, personalized menstrual health information can also be evaluated at home with urinary hormonal measurement. There are now quantitative fertility monitors, which give values of menstrual cycle hormones along with predictive algorithms provided in accompanying smartphone apps [34]. One of these devices, the Mira fertility monitor (Figure 2), measures follicle-stimulating hormone (FSH), estrone-3-glucuronide (E_1_3G), luteinizing hormone (LH), and pregnanediol glucuronide (PDG) in the urine [35].

### 1.4. Correlation with Menstrual Parameters, Serum, and Ultrasound

While there have been unpublished data demonstrating internal validity by the Mira monitor manufacturers, there have not been any formal studies comparing it to the gold standard of the estimated day of ovulation on ultrasound, and serum correlations need to be externally validated. These results should also be contextualized with regard to ovarian reserve with serum anti-Müllerian hormone (AMH) levels [36]. Besides hormonal variations, other key parameters of the menstrual cycle include bleeding patterns and vital sign changes. Bleeding patterns during menses and throughout the cycle are a barometer of menstrual health, and there are multiple bleeding scores to monitor these changes [37], but it is important to use a score that has been validated against a physical measurement of fluid loss like the Mansfield–Voda–Jorgensen Menstrual Bleeding Scale [38].

In addition, temperature changes in the menstrual cycle (i.e., the temperature shift after ovulation, see Figure 1E) have been known for many years and have been used to guide fertility assessment [39,40]. It should be emphasized that these menstrual cycle biomarkers require correlation with the gold standard of serum hormonal measurements and serial endovaginal ultrasound to track follicular development and ovulation. Previous studies have shown that the ultrasound-based day of ovulation is highly correlated with urinary hormones [41,42,43,44]. Our primary objective in this protocol will be to establish this correlation specifically for the Mira monitor.

## 2. Materials and Methods

### 2.1. Objective and Hypothesis

Our objective is to characterize quantitative hormones in the urine using the Mira monitor and validate these in reference to serum hormonal measurements and the gold standard of the ultrasound day of ovulation in participants with normal (regular) menstrual cycles. This will also help to establish external validity for the Mira monitor for use in women with regular cycles, rather than relying on industry-based internal data. We will then compare those with regular cycles to oligomenorrheic women with polycystic ovarian syndrome (PCOS) and oligomenorrheic athletes.

We hypothesize that the Mira monitor’s detected urine hormone pattern will accurately correlate with serum hormonal levels and will predict (LH) and confirm (PDG) the ultrasound day of ovulation in those with regular cycles as well as those with oligomenorrheic cycles.

### 2.2. Design

A prospective cohort with a longitudinal follow-up of participants with regular menstrual cycles and irregular cycles will be established in order to track urinary hormones with serum hormones and confirm ovulation with ultrasound.

### 2.3. Inclusion and Exclusion Criteria

Purposive sampling will be carried out to ensure an ethnically diverse sample reflective of the Canadian population. Table 1 and Table 2 outline the inclusion and exclusion criteria. These participants will be recruited through primary care clinics and university social media advertising along with snowball sampling in the community. Irregular cycles in PCOS will be identified based on historical cycle lengths and variability as well as one other Rotterdam criterion (Table 2). Irregular cycles in athletes will also be identified based on historical cycle lengths and variability, specifically when an athlete has recognized less frequent cycles with their training activities. Athletes will be recruited from known sports research groups locally.

### 2.4. Recruitment and Sample Size Considerations

Recruitment will occur through the University of Calgary social media and research sites. We anticipate that a snowball sampling effect will also occur. Interested participants will be contacted by a research assistant to complete an online survey to ensure they meet the inclusion criteria (Table 1 and Table 2).

Previous ultrasound studies validating urine hormone monitor measurements have targeted 50 participants over 3 cycles, for a total of 150 menstrual cycles [41]. With 150 cycles for analysis, the study would be adequately powered to detect differences of 0.5 days in the estimated day of ovulation, cycle length, and follicular/luteal phase lengths. This calculation was done with G*Power 3.1, with an effect size of 0.2, alpha 0.05, and power of 80%. This calculation is valid for correlation statistics with an a priori power analysis with one tail. Oversampling up to 60 participants may be required to ensure that we have 150 cycles for analysis. The same sample size will be used for recruitment of the PCOS and athlete groups. We know that the participant burden is high, and therefore, we are prepared to continue to recruit until we reach sample size.

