### 2.6. Mira Monitor Testing Protocol

Participants will be given a Mira fertility monitor and enough test wands for three menstrual cycles. The Read Your Body (RYB) App (Figure 3) will need to be downloaded onto participants’ smartphones, and the participants will set up a personal accounts which the investigators will not have access to. The app developers have no way of accessing personally identifying details, nor menstrual cycle data, from the RYB app. Users of the app will have 3–4 months of free use of the App during the study. Email addresses and any other personally identifying details will not be collected by the app team nor by the research team through the app. Over the three menstrual cycles, participants will test daily first-morning urine (using an initial stream catch in a clean cup) with the Mira monitor for menstrual cycle hormones (FSH, E_1_3G, LH, and PDG) as well as take their temperature with a basal body thermometer. Data from the Mira monitor, menstrual cycle observations and bleeding patterns will be entered manually into the Read Your Body App. Bleeding patterns will be recorded with the bleeding score integrated in the app (see Section 2.7), and other observations (intercourse patterns, mucus secretions, open text observations) are also optionally available for manual entry in the app. The app provides cycle summaries and visual graphs of cycle changes to help improve menstrual health literacy for the individual user.

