## 3. Results (Planned)

### 3.1. Data Analysis

Datasets will be analyzed using SPSS version 29 (IBM, Chicago, IL, USA) and charts prepared using SPSS or Excel (Microsoft, Redmond, WA, USA). Descriptive statistics will be used to determine the means, standard deviations (SD), and 95% confidence intervals (CI) of the menstrual cycle parameters, i.e., cycle length, day of ovulation, length of the follicular phase and the luteal phase, menstrual bleeding scores, and duration. The ultrasound-defined day of ovulation (US-DO) will be considered day 0 as a reference for days leading up to and after ovulation. The main analysis in this sample (for which it is powered) will be to correlate (with Spearman’s correlation coefficients) the day of ovulation with peak levels of LH on the Mira monitor, as well as with the day of progesterone elevation, to confirm ovulation. Sensitivity and specificity analyses of each hormone in relation to the US-DO will be calculated.

Secondary exploratory data analyses (not considered in the power calculations) will include daily average hormone values from the Mira monitor referenced to day 0 (US-DO), average hormone values, 95% confidence individuals on days leading up to ovulation (days −5, −4, −3, −2, −1, etc.), and after ovulation (days +1, +2, +3, +4, +5 etc.) from cycle day 6 until the end of the cycle. Daily means, SDs, and CIs of hormone values across the study sample will be used to describe the variability in the population, as was done in the pilot study [34], and individual (personalized) hormone patterns will also be considered as we have presented in previous studies [51]. Day-to-day hormone variability will require complex modelling of hormonal patterns, which we have used in previous studies [53], using *R*-software (*R* Foundation for Statistical Computing, Vienna, Austria). The specific statistical methods involve creating best-fit distributions for wave patterns of the hormones using the mean square of residuals as the loss function, with the goal to minimize the loss function to improve the fit of the distribution based on the density of the hormone wave patterns in the population; this specific method has helped to identify distinct hormone patterns that may represent different physiologic mechanisms, but it must be emphasized that these are hypothesis-generating rather than primary endpoints of this proposal.

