### 3.2. Pitfalls and Mitigation Strategies

Frequent endovaginal ultrasounds may not be acceptable for the duration of the three cycles of use being requested of participants. To mitigate this, we will use trained ultrasound technologists and a patient-centered approach to provide participants with an acceptable level of discomfort during the procedure. A research assistant will follow up to ensure that ultrasound schedule reminders are provided to avoid missing follicular scans. During recruitment, we will seek subjects who would feel comfortable with this frequency of ultrasounds. We will oversample up to 60 participants, as stated earlier, to ensure we can have 150 cycles for analysis to achieve the appropriate power for our study.

Correlating progesterone changes with temperature and ultrasound-confirmed ovulation will help to validate progesterone as a confirmation of ovulation. Some studies have identified inconsistencies in specific PDG levels in the confirmation of ovulation [54], while other studies with ultrasound-confirmed ovulation have been able to identify relevant PDG levels to confirm ovulation [55].

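### The 80% power in section 2.4 requires 150 independent cycles, but the 150 are three cycles from each of about 50 women

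*Protocol article*

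**What the plan says.** Protocol article, section 2.4, starts from previous studies that "have targeted 50 participants over 3 cycles, for a total of 150 menstrual cycles" and takes over the total: "With 150 cycles for analysis, the study would be adequately powered to detect differences of 0.5 days" in ovulation day, cycle length and phase lengths. It then gives the basis: "This calculation was done with G*Power 3.1, with an effect size of 0.2, alpha 0.05, and power of 80" percent, and adds "This calculation is valid for correlation statistics with an a priori power analysis with one tail".

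The allowance for loss is also counted in cycles. "Oversampling up to 60 participants may be required to ensure that we have 150 cycles for analysis", and section 3.2 repeats that the purpose is "to ensure we can have 150 cycles for analysis to achieve the appropriate power for our study". The PCOS and athlete groups take the same sample size.

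Section 2.6 makes the repeated structure plain: "Over the three menstrual cycles, participants will test daily first-morning urine".

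Section 3.1 names Spearman coefficients between ovulation day and the LH peak, and with the day of progesterone elevation, as the analysis the sample is powered for. It adds sensitivity and specificity, and says "Descriptive statistics will be used to determine the means, standard deviations (SD), and 95% confidence intervals (CI) of the menstrual cycle parameters". Neither section mentions an ICC, a design effect or the participant as a cluster. The modelling in R in section 3.1 is exploratory curve fitting of hormone patterns and does not deal with repeated cycles.

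**The concern.** The power routine was given 150 as a number of independent pairs, but the study will have about 50 independent women. Cycles from the same woman tend to resemble each other in length, in ovulation day and in phase lengths, so a second or third cycle adds less information than a cycle from a new woman. The stated 80% is then an upper limit that is reached only with no within-woman correlation.

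The same applies to precision. If the means, correlations, sensitivities and specificities are given intervals that treat cycles as independent, those intervals will be too short. Section 3.3 expects the results to supply nomograms and reference values for later studies, so overstated precision would be carried forward.

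**Working it through.** **Inputs.** From section 2.4: r = 0.2, one-tailed alpha 0.05, power 80%, N = 150 cycles, and 50 women with m = 3 cycles each. The documents give no ICC, so 0.1, 0.3 and 0.5 are assumed.

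**Reproducing the plan's figure.** For N independent pairs, the noncentral-t form of the correlation test has noncentrality r/√(1−r²) × √N. With r = 0.2 and N = 150 this is 0.2041 × 12.247 = 2.50, and one-sided power is 80.1%. Solving for 80% gives N = 149.8, so 150. The Fisher z form with its bias term gives 79.4% at 150 and N = 153. Other readings do not fit: a two-sided correlation needs 191 to 194, and a one-sided paired t-test at d = 0.2 needs 156. The 150 is therefore the independent-pairs answer for a correlation.

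**Correlation with clustering.** When both variables are clustered within women, the variance of the coefficient is inflated by about 1 + (m−1) × ICCx × ICCy = 1 + 2 × ICCx × ICCy. With the same ICC in both:

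| ICC | Design effect | Effective N | Power |
|---|---|---|---|
| 0 | 1.00 | 150 | 80.1% |
| 0.1 | 1.02 | 147.1 | 79% |
| 0.3 | 1.18 | 127.1 | 74% |
| 0.5 | 1.50 | 100 | 65% |

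The Fisher z form gives 79%, 73% and 64%. As a check, Spearman's coefficient was simulated for 50 × 3 cycles with r = 0.2. The standard deviation of its Fisher z was 0.0821 at ICC 0, 0.0901 at 0.3 and 0.1004 at 0.5. The variance ratios are (0.0901/0.0821)² ≈ 1.20 and (0.1004/0.0821)² ≈ 1.50, against 1.18 and 1.50 from the formula.

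**Means with clustering.** For cycle length, phase lengths and ovulation day, the design effect is 1 + (m−1) × ICC = 1 + 2 × ICC. Effective n is 150 divided by it, and the interval must widen by its square root:

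| ICC | Design effect | Effective n | Width factor | Coverage of naive 95% CI |
|---|---|---|---|---|
| 0.1 | 1.2 | 125 | 1.10 | about 93% |
| 0.3 | 1.6 | 94 | 1.26 | about 88% |
| 0.5 | 2.0 | 75 | 1.41 | 83–84% |

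Coverage was simulated with 20,000 trials of 50 × 3 and agrees with the normal approximation.

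**Does oversampling cover it?** 60 × 3 = 180 possible cycles, and 150/180 = 83.3%, so the margin allows for 16.7% loss. The target remains 150 analysable cycles. If these came from more than 50 women, with fewer cycles each, the design effect would be somewhat smaller. For example, 30 women with three cycles and 30 with two give (30×9 + 30×4)/150 = 2.6 in place of m, so the factor for means is 1 + 1.6 × ICC. That softens the loss but does not remove it.

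**The case against.** The best defence is that the main analysis is hardly threatened. Section 1.4 reports that earlier studies found ultrasound ovulation day highly correlated with urinary hormones. With a true correlation of 0.9 (assumed), simulation of 50 × 3 cycles gives power near 100% against zero at every ICC tried. A naive Fisher z interval for Spearman's coefficient covers about 94–95% at ICC 0.3 and 91–93% at 0.5. This stands: in that setting the harm is to interval width, and for the correlation it is modest.

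It is also fair that section 3.1 does not say how intervals will be computed, and that an article may leave this to an analysis plan. The point about intervals is therefore conditional. The power statement in 2.4 is not, because a later plan cannot make it true.

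A reader might be tempted to go further in four ways that the documents do not support.

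- **Power of about 61% and 53% at ICC 0.3 and 0.5.** These come from a one-sided paired t-test on means at d = 0.2 with design effect 1 + 2 × ICC. Section 2.4 states a correlation, and section 3.1 names no test of mean differences.
- **An inflated type I error.** A naive one-sided 5% Spearman test rejects in about 6% and 9% of simulated trials at ICC 0.3 and 0.5, but only if LH-peak day and ovulation day are uncorrelated. Section 1.4 makes that implausible.
- **Intervals that are certainly too narrow.** Section 3.1 does not fix the method.
- **The consistent-cycle criterion in Table 1 as an acknowledgement of within-woman correlation.** The article uses it to define the regular group and gives no such reason.

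**Conclusion.** The concern holds for the sample-size statement. The stated inputs give 80% power at 150 only under independence, and the design does not provide independence. Power for the stated correlation is about 79%, 74% and 65% at ICC 0.1, 0.3 and 0.5 in both variables. For mean cycle parameters, the effective sample is 125, 94 and 75, and intervals that ignore clustering would need to be 10%, 26% and 41% wider. These sizes rest on assumed ICCs, three cycles from each of 50 women, and approximate design effects. The part on intervals applies only if cycles are analysed as independent, which section 3.1 neither states nor excludes. With a high true correlation, the primary test against zero is safe. Should-fix.

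**What to change.** In section 2.4, say that cycles are nested in women. Report power and effective sample size over a stated ICC range, for example 0.1 to 0.5, using 1 + 2 × ICCx × ICCy for the correlation and 1 + 2 × ICC for means. This corrects the claim and does not require more participants.

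In section 3.1, name the participant as the cluster. Obtain intervals for the Spearman coefficients and for sensitivity and specificity from a bootstrap that resamples participants with all their cycles. Obtain intervals for mean cycle parameters from a model with a random participant intercept, or from a cluster-robust variance. Apply the same in the PCOS and athlete groups.

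The cost is a few lines of text and of R code, which the study already plans to use, and no new data. The downside is a less favourable stated power and moderately wider intervals, about 10–41% for means over ICC 0.1 to 0.5.

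### The claimed power for 0.5-day differences does not follow from the sample-size calculation, which is for a correlation of 0.2 and contains no quantity in days

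*Protocol article*

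**What the plan says.** Section 2.4 takes its target from earlier ultrasound validation studies, which "have targeted 50 participants over 3 cycles, for a total of 150 menstrual cycles". It then says: "With 150 cycles for analysis, the study would be adequately powered to detect differences of 0.5 days in the estimated day of ovulation", and lists cycle length and the two phase lengths alongside.

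The next two sentences describe the supporting calculation: "This calculation was done with G*Power 3.1, with an effect size of 0.2, alpha 0.05, and power of 80" per cent, and "This calculation is valid for correlation statistics with an a priori power analysis with one tail".

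Section 3.1 names the analysis that the calculation serves: "The main analysis in this sample (for which it is powered) will be to correlate (with Spearman’s correlation coefficients) the day of ovulation" with the LH peak on the monitor and with the day of progesterone elevation.

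The article gives no SD in days, no test of a mean difference in days, and no step from 0.2 to 0.5 days.

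**The concern.** The paragraph attaches one calculation to two different properties. The first is sensitivity to half a day in four timing parameters. The second is power for a correlation. These are different quantities, and one cannot be converted into the other without a variance in days and a named test.

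This is the article's only sample-size justification. A reader will take from it that half-day sensitivity has been shown for ovulation day, cycle length and both phase lengths. A later comparison in days that finds nothing could then be read as evidence that no half-day difference exists, when the design has not been shown to have that sensitivity.

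**Working it through.** **Inputs.** From section 2.4: 150 cycles (50 participants, 3 cycles each), effect size 0.2, alpha 0.05, one tail, 80% power, target difference 0.5 days. From section 3.1: the powered analysis is a Spearman correlation. Not given: the kind of effect size, the null value, any SD in days, and the correlation between cycles of the same participant.

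**Step 1: reproduce the 150.** Take 0.2 as a correlation tested against zero, one-tailed at 0.05.

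- Point-biserial t test, N − 2 degrees of freedom, noncentrality r/√(1 − r²) × √N = 0.2/√0.96 × √150 = 2.50. Power at 150 is 80.1%, and 150 is the smallest N that reaches 80%.
- Fisher z: N = ((1.645 + 0.842)/atanh(0.2))² + 3 = 153.4, so 154. Power at 150 is 79.2%.
- Bivariate normal, by simulation: N = 153. Power at 150 is 79.4%.
- Two-tailed, the point-biserial and Fisher z methods need 191 and 194. The one-tailed setting is therefore needed to arrive at 150.

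The stated number is reproduced as a one-tailed correlation calculation.

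**Step 2: look for days in it.** The noncentrality in step 1 depends only on r and N. Spearman's coefficient depends only on ranks, and adding a constant to one variable leaves its ranks unchanged. In a simulated example with 150 pairs, rho was 0.930 with no shift, 0.930 with a 0.5-day shift and 0.930 with a 3-day shift. The powered test cannot respond to the kind of difference claimed.

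**Step 3: try the most favourable alternative.** Read 0.2 as a standardised paired difference, so that SD = 0.5/0.2 = 2.5 days. The paired t test has noncentrality 0.2 × √150 = 2.45. Power at 150 is 78.6% one-sided and 68.2% two-sided, and 80% needs 156 or 199 cycles. For other assumed SDs of the paired difference, with 150 independent cycles and a 0.5-day difference:

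| Assumed SD (days) | One-sided power | Two-sided power |
|---|---|---|
| 1.5 | 99% | 98% |
| 2 | 92% | 86% |
| 2.5 | 79% | 68% |
| 3 | 65% | 53% |
| 4 | 45% | 33% |

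Reaching 80% requires an SD of at most about 2.45 days one-sided or 2.17 days two-sided.

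**Step 4: independence.** Every figure above treats the 150 cycles as independent. With three cycles per participant, an approximate design effect is 1 + 2 × ICC. At assumed ICCs of 0.2, 0.5 and 0.8, the effective N is 150/1.4 = 107, 150/2 = 75 and 150/2.6 = 58. Fisher z power for a correlation of 0.2 is then about 66%, 53% and 44%.

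**Step 5: precision in days.** The 95% CI half-width for a mean difference is 1.96 × SD/√150 = 0.16 × SD if cycles are independent. At an assumed ICC of 0.3 it is 0.16 × √1.6 × SD = 0.20 × SD.

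**The case against.** The best defence is that the main analysis is powered as section 3.1 says: the powered analysis is a correlation, and the arithmetic for a correlation is right, apart from the independence of cycles. That stands. Neither the sample size nor the planned analysis is shown to be wrong by this point.

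The second defence is that the article names neither the G*Power routine nor the type of effect size, and that a paired reading of 0.2 comes within 1.4 points of 80% (78.6%, one-sided). The SD behind it might be in the fuller protocol. This has some force: the null of zero is an inference, and with an SD of paired differences of 1.5 to 2 days the study would in fact have 92% to 99% one-sided power. But the paired reading needs 156 cycles rather than 150, and it contradicts the article's own description of the calculation as one for correlation. It would also need a single SD to serve four parameters. A missing SD is not the charge. The charge is that the stated claim and the stated calculation do not match.

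Three stronger readings may tempt a reader, and the article does not support them:

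- **The between-group comparisons are underpowered for 0.5 days.** The article says "The same sample size will be used for recruitment of the PCOS and athlete groups", which promises a number of participants and not a detectable difference. No 0.5-day claim between groups is made, and section 3.1 attaches no power to one.
- **The one-tailed test conflicts with the 95% CIs.** Those intervals are for descriptive means and daily hormone values. A one-tailed test of a correlation expected to be positive does not contradict them.
- **A nearly worthless monitor could be declared valid.** Nowhere is rejection of a zero correlation made the criterion for validation, and sensitivity and specificity against ultrasound are also planned.

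**Conclusion.** The point holds in a limited form. The 150 is correct for a one-tailed test of a correlation of 0.2 (80.1% by the point-biserial routine, 79.2% by Fisher z), on the inference that the null is zero and on the assumption that cycles are independent. The claim of adequate power for 0.5-day differences in four parameters does not follow from it.

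No single figure can replace the claim, because the article gives no SD in days. On the paired reading, one-sided power lies between 99% and 45% for assumed SDs of 1.5 to 4 days, and is about 79% at the implied 2.5 days. It would therefore be wrong to infer that the study cannot detect half a day. It may be able to for the monitor-versus-ultrasound comparison, but the stated calculation does not show this.

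**What to change.** Choose one of two changes to section 2.4.

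1. Delete the 0.5-day claim and state what the calculation delivers: about 80% power, one-sided at alpha 0.05, for a correlation of 0.2 (against zero, if that is the null intended), with the 150 cycles treated as independent. Add that power is lower once the three cycles per participant are taken into account, so that the 80% is not printed without its condition.
2. Keep a 0.5-day statement, but support it with a separate calculation for each parameter, giving the SD, the test and its sidedness.

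Optionally, add the precision that 150 cycles give for the mean difference in days between the monitor's and the ultrasound day of ovulation: a 95% CI half-width of 0.16 × SD if cycles are independent, or 0.20 × SD at an assumed ICC of 0.3.

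The first option costs the rewording of one paragraph and a less favourable stated figure. The second also needs a sourced SD for each parameter. Neither changes enrolment: the target of 150 cycles and the allowance for up to 60 participants can stay as they are.
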